This manuscript describes the protocol for a study to evaluate the CVS diagnostic performance in a population of unselected suspected stroke arriving at a UK HASU. Whilst the most important future use for the CVS is likely to be in the pre-hospital setting, conducting research evaluations in this context is particularly challenging and prior to embarking on such a study, there needs to be preliminary data of accuracy in a comparable population. This can be achieved by obtaining CBA readings undertaken by trained hospital staff from patients with a paramedic assigned diagnosis of suspected stroke immediately following hospital admission and before specialist or radiological diagnosis is made. This research is timely and topical because finding an accurate, portable and potentially widely available point of care diagnostic for LVO or complex stroke would revolutionise stroke care.

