#### Data related to the first 24 h of admission

Data for confirmation of inclusion and exclusion criteria:

Demographic information (age); date/time of hospital attendance; confirmation of admission by ambulance (yes/no); confirmation that ambulance personnel suspected stroke (yes/no); symptom onset or last known to be well date/time (hospital judgement); first recorded conscious level on arrival at hospital (AVPU scale); first blood glucose reading on admission (capillary or serum glucose); confirmation of other inclusion and exclusion criteria (e.g. brain imaging will be performed, absence of electro-stimulating devices in the head and neck).

Other data related to day 1 of admission:

Demographic information (gender); symptoms suggesting possible stroke according to the ambulance clinician (facial weakness; arm weakness; speech disturbance; other); side of symptoms according to the ambulance clinician (left/right/both/not applicable, e.g. speech); first blood pressure reading on admission; first heart rate reading on admission; first body temperature reading on admission; first peripheral oxygen saturation on admission; ECG rhythm (presence of atrial fibrillation); stroke symptom severity as soon as possible after arrival (National Institute of Health Stroke Score (NIHSS) including all component scores [7]); time of NIHSS completion; clinical stroke type according to new symptoms (Oxford Community Stroke Project classification including left/right lateralisation as appropriate [26]); previous medical history from healthcare records (stroke; head injury; intracranial surgery; TIA; atrial fibrillation; diabetes; hypertension; hyperlipidaemia); if a previous stroke was recorded, had it resulted in permanent arm or leg weakness (no; yes left; yes right; yes both), or any permanent speech difficulty (yes or no); current use of anticoagulant medication; pre-stroke modified Rankin Score [27]; pre-stroke walking ability (independent; walking aid; physical assistance from one person; unable to walk at all); diagnosis listed after completion of initial assessments (stroke/non-stroke (if non-stroke free text for diagnosis); thrombolysis treatment administered (yes/no); date/time of bolus administration (if thrombolysis received); mechanical thrombectomy treatment administered (yes/no); date/time of arterial puncture (if thrombectomy received).

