This is an exploratory objective, and as such the analyses will be data-driven and dependent on results for objectives 1 and 2. Proposed investigations focus on three main areas: (i) whether available clinical data might be incorporated to improve the diagnostic accuracy of the CVS; (ii) variations in specification of the reference diagnosis for LVO, and (iii) patient subgroup analyses to identify whether the CVS may perform better in some clinical settings than others.
(i)Clinical covariates: key variables will be added to the logistic regression models described in objectives 1 and 2 to see if this could significantly increase the accuracy of the prediction of the model. Clinical variables that would be available to ambulance personnel or staff involved in urgent assessment at the hospital will be included to reflect those available at the point of testing. Multivariate logistic regression will be conducted, with diagnosis (complex stroke OR LVO) as the outcome (*y*) and CBA measurement along with variables considered to be of possible clinical importance (such as gender, age, NIHSS) as the explanatory variables (*x*1, *x*2, *x*3, …). A stepwise variable selection procedure will be used, and only variables that significantly improve the ROC AUC will be retained in the model. Sensitivity, specificity, ROC AUC (with confidence intervals) and threshold will be reported if a suitable model is found.(ii)Alternative definitions for LVO: the diagnostic accuracy of CBA measurement will be assessed by modelling as described for objective 1, where the reference diagnosis will be assigned as follows:

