#### Sample size

The future intended purpose of CBA measurement is to ‘rule in’ patients with complex stroke and/or LVO from the suspected stroke population. The sample size calculation is therefore based on the detection of test specificity. ‘Rule in’ is chosen as the test results would be used to redirect individuals to a neuroscience centre for highly specialist care. Suspected stroke patients without a diagnosis of complex stroke or LVO do not need transportation to a neuroscience centre and should be admitted to the nearest local hospital.

Reported frequencies for LVO, large intracerebral haemorrhages and prior territorial stroke are 27%, 3% and 4% respectively amongst the unselected population with suspected stroke. There are no reliable estimates for the frequency of SSAVS in the unselected UK population—it is an uncommon finding and previous cohorts of LVO patients are likely to have included cases with high degrees of symptomatic stenosis without reporting them separately. Therefore, using the above-reported frequencies and a minimum specificity of 70% from the diagnostic test, alpha = 0.05 and beta = 0.1:
One hundred twelve participants would detect a specificity of 85% (95%CI: 70%–100%) for complex stroke (i.e. LVO + SSAVS + LICH + PTS) versus all other outcomes in the suspected stroke population (i.e. small/medium intracerebral haemorrhage + ischaemic stroke without LVO + TIA + mimic condition).
One hundred one participants would detect a specificity of 85% (95%CI: 70%–100%) for ischaemic stroke due to LVO versus all other outcomes in the suspected stroke population (i.e. SSAVS + LICH + PTS + small/medium intracerebral haemorrhage + ischaemic stroke without LVO + TIA + mimic condition).

In terms of sensitivity, the 112 participants would detect sensitivity of 85% (95%CI: 63%–100%) for complex stroke and 85% (95%CI: 61%–100%) for LVO.

As outlined above, some enrolled participants may not provide data for inclusion in the analyses and this lack of data is difficult to estimate. The initial recruitment target is inflated for 10% data exclusion (124 participants) but prospective monitoring of the number of cases which can contribute to the analyses will occur and fewer or additional participants will be sought if required.

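### Objective 3(i) selects from ambulance-available and hospital-measured variables in one pool, so a retained hospital variable would leave the pre-hospital question unanswered

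*Protocol article*

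**What the plan says.** Under Statistical analysis, Objective 3(i), the protocol article asks whether clinical data can improve the accuracy of the cerebral bioimpedance asymmetry (CBA) reading. On the candidates it states: "Clinical variables that would be available to ambulance personnel or staff involved in urgent assessment at the hospital will be included". The rest of that sentence gives the reason, which is to match what is on hand where the test is done. The model has "CBA measurement along with variables considered to be of possible clinical importance (such as gender, age, NIHSS) as the explanatory variables". Selection is by one rule: "A stepwise variable selection procedure will be used, and only variables that significantly improve the ROC AUC will be retained in the model". Reporting is conditional and in the singular: "Sensitivity, specificity, ROC AUC (with confidence intervals) and threshold will be reported if a suitable model is found". The objective is labelled exploratory and data-driven.

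On intended use, the Background says "the most important future use for the CVS is likely to be in the pre-hospital setting", and the Sample size section says "the test results would be used to redirect individuals to a neuroscience centre for highly specialist care". The Background also names a second benefit, sparing some angiography at a local hyperacute stroke unit (HASU).

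On timing, the list of data for the first 24 hours records NIHSS as "stroke symptom severity as soon as possible after arrival". Objective 3(ii) likewise treats it as a hospital score when deriving RACE from it. The same data list includes "symptoms suggesting possible stroke according to the ambulance clinician (facial weakness; arm weakness; speech disturbance; other"), together with the side of symptoms as judged by the ambulance clinician.

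**The concern.** The protocol has two settings in view, the ambulance and the hospital, and they do not share the same information. The selection rule ignores this difference: a variable stays if it raises the AUC, wherever it was measured. A full severity score taken in hospital is a natural candidate to be retained.

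If it is retained, the final model needs an input that this study obtains only after arrival. Its sensitivity, specificity and threshold then describe a hospital decision. Whether face, arm and speech signs and their side help the CBA reading before hospital would not be reported, because no model restricted to them is specified. The study is presented as preliminary evidence ahead of pre-hospital work, and that is the question such work would start from.

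**Working it through.** **1. Text side by side.**

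| Item | Where | What it fixes |
|---|---|---|
| Candidate pool | Objective 3(i) | Ambulance or hospital variables, together |
| Retention rule | Objective 3(i) | Significant AUC gain only |
| Output | Objective 3(i) | One model, if a suitable one is found |
| NIHSS timing | Data, first 24 h; Objective 3(ii) | After arrival, in hospital |
| Ambulance signs and side | Data, first 24 h | Collected |
| Main future use | Background; Sample size | Pre-hospital redirection |
| Second use | Background | Local HASU |

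No entry requires a model limited to ambulance-available variables.

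**2. What the plan quantifies.** It gives no figure for the covariate model, so there is none to reproduce. Only the case numbers follow from it. Complex stroke: 27% + 3% + 4% = 34%, and 112 × 0.34 ≈ 38 (stenosis cases would add an unknown number). LVO: 112 × 0.27 ≈ 30.

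**3. Size of the gap, by assumption.** The AUCs below are assumed. Take binormal predictors with d = √2 × Φ⁻¹(AUC) and within-group correlation r between CBA and the added predictor. The combined separation is D² = (d₁² − 2r·d₁d₂ + d₂²)/(1 − r²), and the combined AUC is Φ(D/√2).

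Central case, r = 0:
- CBA 0.80: d = 1.190, d² = 1.417. NIHSS 0.80: the same. Ambulance signs 0.65: d = 0.545, d² = 0.297.
- CBA + NIHSS: D² = 2.833, AUC = 0.883.
- CBA + signs: D² = 1.714, AUC = 0.823.
- Gap: 6.0 AUC points.

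The same formula with other assumptions (one r for both added predictors):

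| CBA | NIHSS | Signs | r | CBA + NIHSS | CBA + signs | Gap (points) |
|---|---|---|---|---|---|---|
| 0.80 | 0.80 | 0.65 | 0 | 0.883 | 0.823 | 6.0 |
| 0.80 | 0.80 | 0.65 | 0.3 | 0.852 | 0.803 | 4.9 |
| 0.80 | 0.80 | 0.65 | 0.5 | 0.834 | 0.800 | 3.4 |
| 0.80 | 0.85 | 0.60 | 0 | 0.909 | 0.810 | 9.9 |
| 0.80 | 0.75 | 0.70 | 0 | 0.860 | 0.839 | 2.0 |
| 0.80 | 0.70 | 0.65 | 0 | 0.839 | 0.823 | 1.7 |
| 0.80 | 0.70 | 0.65 | 0.5 | 0.802 | 0.800 | 0.2 |
| 0.90 | 0.70 | 0.65 | 0 | 0.917 | 0.910 | 0.7 |

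**4. Effect on specificity at 70% sensitivity**, by Φ(D − 0.524), with CBA 0.80 and NIHSS 0.70:
- CBA alone: Φ(1.190 − 0.524) = 75%.
- Adding NIHSS, r = 0: D = √(1.417 + 0.550) = 1.402, giving 81%.
- Adding NIHSS, r = 0.5: still 75%.

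So NIHSS can carry a model past the 80% specificity that the plan asks of CBA in Objectives 1 and 2, or can add almost nothing.

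**The case against.** The authors did apply an availability rule: candidates are meant to match the point of testing, and in this study testing is done in hospital by trained hospital staff. A model with hospital variables fits that setting and serves the local HASU use directly. The objective is exploratory, further exploratory analyses are allowed, and nothing says the covariate model will steer ambulances. The article gives only example variables, so an analysis plan that is not shown could split the list by setting. Another data-driven model on about 38 or 30 cases is not free.

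Much of this stands. The pooled model is legitimate for hospital use, and the exploratory label limits the consequences. It does not settle the point, because the article states one pool, one retention rule and one reported model. That is a choice already made, not a detail left open. An exploratory label also does not tell a reader which setting a model serves.

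A reader might infer more than the documents support:
- **That crews cannot reach the reported accuracy.** This depends on a hospital-measured variable being retained. Age, gender and ambulance-recorded signs raise no such difficulty.
- **That NIHSS is hospital-only in general.** The protocol shows only that it is scored in hospital here. It does not say that crews could not score it.
- **That NIHSS will displace the ambulance signs.** This is plausible, but it is a prediction.

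**Conclusion.** The point holds in conditional form. One stepwise selection mixes variables from two settings. If a hospital-measured one is retained, the reported accuracy applies to hospital or HASU use and may not carry over to the pre-hospital redirect decision. The value of the ambulance-recorded signs without it would go unreported.

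The size cannot be derived from the documents. Under the assumptions shown, the gap runs from 0.2 to 9.9 AUC points. It shrinks when CBA alone is already strong, when NIHSS is little better than the ambulance signs, or, in most of the cases shown, when the predictors are correlated with CBA.

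It would be wrong to conclude that the main results are compromised. Objectives 1 and 2, their 80% and 70% criteria and the sample size concern CBA alone. This is a worthwhile improvement to an exploratory analysis, not a flaw in the study's main conclusions.

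**What to change.** In Objective 3(i), specify two exploratory candidate sets for each target (complex stroke and LVO):
- **(a) Pre-hospital:** CBA, age, gender, and the ambulance-recorded symptoms and side.
- **(b) Hospital:** set (a) plus NIHSS and other admission findings.

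Report both, label each with the setting where its inputs exist, and base any statement about pre-hospital use on (a) only. If two sets were already intended, one clarifying sentence is enough.

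The cost is a short change of wording and one more data-driven model per target, on about 38 complex-stroke or 30 LVO cases. That model should be reported as exploratory. All the variables named are already collected.

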	Symptomatic severe anterior vessel stenosis	CT/MR angiography assessed by blinded neuro-radiologist which shows ≥ 70% narrowing of any large branch of the anterior cerebral circulation (ICA or MCA) without occluding thrombus, the side of the focal neurological symptoms suffered by the patient is compatible with stenosis, the severity of focal symptoms is ≥ 6 on NIHSS.
Minor Stroke	Small / medium volume intracerebral haemorrhage	Brain imaging assessed by blinded neuro-radiologist. Haematoma volume < 60ml in a single cerebral hemisphere.
	Ischaemic stroke without large vessel occlusion	Expert clinician diagnosis at 72 hours after hospital admission (or discharge/death if sooner), CTA/MRA confirms the absence of LVO (i.e. Clot Burden Score = 10), and CTA/MRA plus clinical findings confirm the absence of SSAVS.
Non Stroke	Transient ischaemic attack	Expert clinician diagnosis at 72 hours after hospital admission (or discharge/death if sooner) and brain imaging findings do not refute the clinician opinion or indicate the presence of one of the other acute outcomes.
	Mimic condition	Expert clinician diagnosis at 72 hours after hospital admission (or discharge/death if sooner) and brain imaging findings do not refute the clinician opinion or indicate the presence of one of the other acute outcomes.

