#### SSAVS outcome state

SSAVS will be defined as present if (a) CT or MR angiography has been conducted and this demonstrates that there is ≥ 70% narrowing of any large branch of the anterior cerebral circulation (internal carotid artery or middle cerebral artery) without occluding thrombus, (b) the side of the focal neurological symptoms suffered by the patient are in keeping with the imaging (e.g. the stenosis is present in the circulation on the left and the symptoms were on the right), and (c) the severity of the focal symptoms is ≥ 6 on the NIHSS scale (measured on admission).

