**Table 2 Tab2:**
[figure not shown]

[figure not shown]

[figure not shown]
Pre-defined primary diagnosis framework

Ischaemic stroke without LVO will be defined as present if the expert clinician considers the patient to have a ‘definite’ or ‘probable’ ischaemic stroke, CT/MR angiography confirms the absence of LVO (i.e. clot burden score = 10), and CT/MR angiography plus clinical findings confirm the absence of SSAVS.

It is possible that there will be participants with a clinical diagnosis of ischaemic stroke who do not undergo CT/MR angiography for some reason (e.g. due to agitation). In these cases, the LVO and SSAVS status are unknown. Data from these participants will not be included in any analysis of operating characteristics but their clinical and radiological information and CBA data will still be reported.

A transient ischaemic attack will be defined as present if the clinician records any ‘definite’ or ‘probable’ TIA diagnosis using the pre-defined framework and brain imaging does not contain findings that refute this opinion or indicate the presence of one of the other acute outcomes. If there is any disagreement between the blinded neuro-radiological review of imaging performed and a clinical diagnosis of TIA, the imaging diagnosis will be used to determine the outcome but such discrepancies will also be reported.

A stroke mimic condition will be defined as present if the clinician records any ‘definite’ or ‘probable’ non-stroke/non-TIA diagnosis using the pre-defined framework and brain imaging is compatible (e.g. tumour) plus does not contain findings which indicate the presence of one of the other acute outcomes. If there is any disagreement between the blinded neuro-radiological review of imaging performed and a clinical diagnosis of mimic condition, the imaging diagnosis will be used to determine the outcome but such discrepancies will also be reported.

If a clinician records an ‘unclear’ diagnosis for any patient and this cannot be resolved, these participants will not be included in any analyses of operating characteristics as it has not been possible to determine an outcome. Available data for these participants will still be reported.

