### Statistical analysis

Objective 1: To determine the diagnostic accuracy of CBA measurement performed using the CVS to identify complex stroke (ischaemic stroke with LVO or SSAVS or LICH ≥ 60 ml in volume or PTS) in patients arriving at the hospital with a paramedic assigned diagnosis of suspected acute stroke.

In the recently published work using this technology, a threshold of CBA = 10 was derived as optimal for identification of complex stroke [21]. This threshold will be validated on the data collected in this study and considered acceptable if it results in specificity of at least 80% and sensitivity of at least 70%. These values have been chosen as clinically important and stringent, to allow validation to be conducted. Sensitivity and specificity will be reported with 95% confidence intervals.

However, the population to be recruited in this study may differ from the earlier work (e.g. less time has elapsed since stroke onset). Therefore, the threshold of CBA = 10 may not result in meeting the criteria described above. If this is the case, a new threshold will be estimated. Univariate logistic regression analysis with diagnosis (complex stroke) as the outcome (*y*) and CBA measurement as the explanatory variable (*x*) will be used to construct an empirical receiver operating characteristic (ROC) curve for all possible thresholds. A new threshold will be chosen to maximize specificity while aiming to maintain a clinically acceptable level of sensitivity (70% in this instance). Sensitivity, specificity and ROC area under curve (AUC) (with confidence intervals) will be reported for the chosen threshold.
2.Objective 2: To determine the diagnostic accuracy of CBA measurement performed using the CVS to identify LVO in patients arriving at the hospital with a paramedic assigned diagnosis of suspected acute stroke.

For this objective, analyses as described above for objective 1 will be conducted, i.e. a threshold of CBA = 10 will initially be evaluated but a new threshold may be estimated if CBA = 10 does not result in sensitivity and specificity meeting the stated criteria.
3.Objective 3: To explore key clinical and radiological influences upon the diagnostic accuracy of CBA measurement for complex stroke and LVO.

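### Objective 3(i) offers NIHSS as a predictor of complex stroke although NIHSS of 6 or more is part of the SSAVS definition, so part of any gain credited to NIHSS is definitional (probably a small part)

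*Protocol article*

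**What the plan says.** **The model.** Statistical analysis, Objective 3(i), adds clinical variables to CBA in a logistic regression "with diagnosis (complex stroke OR LVO) as the outcome". The candidates are "variables considered to be of possible clinical importance (such as gender, age, NIHSS) as the explanatory variables". Selection is stepwise, and a variable stays only if it significantly improves the ROC AUC. Sensitivity, specificity, AUC and threshold are reported for a suitable model. Objective 3 is labelled exploratory and data-driven.

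**The outcome.** Objective 1 sets out "to identify complex stroke (ischaemic stroke with LVO or SSAVS or LICH" of at least 60 ml, or PTS.

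**The SSAVS criteria.** The section SSAVS outcome state requires (a) narrowing of at least 70% without occluding thrombus, (b) a compatible symptom side, and (c) that "the severity of the focal symptoms is ≥ 6 on the NIHSS scale (measured on admission". Table 1 repeats criterion (c): "the severity of focal symptoms is ≥ 6 on NIHSS".

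**The NIHSS collected.** The first-24-hour data list one score: "stroke symptom severity as soon as possible after arrival (National Institute of Health Stroke Score (NIHSS) including all component scores".

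**The other side of the cut.** Ischaemic stroke without LVO requires, among other things, that "CT/MR angiography plus clinical findings confirm the absence of SSAVS". A low NIHSS is one way for SSAVS to be absent.

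**The concern.** The same admission score is a candidate predictor and a required part of the reference standard for one component of the outcome. For some patients the model would be credited with predicting a label that the score itself assigned. The retention rule counts that credit as improved AUC, and the model's reported accuracy carries it.

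At stake is how Objective 3(i) is read. It asks whether clinical data can improve the diagnostic accuracy of the device. If adding NIHSS to CBA raises the AUC for complex stroke, the report could not say how much of the rise is diagnostic information and how much is the definition.

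The overlap goes no further. LVO, LICH and PTS are defined by imaging alone, so the LVO covariate model has no such overlap. Objectives 1 and 2 use CBA only.

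**Working it through.** The plan gives no accuracy figure for the covariate model, so there is none to reproduce. The denominator of 112 is not in dispute. An exact one-sided 0.05 test of 70% against 85% with 90% power needs 73 non-cases, and 73 / (1 − 0.34) = 110.6, so 111, one below the stated 112.

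**Step 1: trace the label.** Take patients with side-compatible stenosis of 70% or more and no LVO or LICH, and apply the outcome state attribution process.

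| NIHSS | PTS | State assigned | Complex? |
|---|---|---|---|
| ≥ 6 | absent | SSAVS | yes |
| ≥ 6 | present | SSAVS | yes |
| < 6 | present | PTS | yes |
| < 6 | absent | ischaemic stroke without LVO, TIA or another non-complex state | no |

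NIHSS decides the class only where PTS is absent. There it separates cases from non-cases by definition.

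**Step 2: count the patients.** The sample size section gives LVO 27%, LICH 3% and PTS 4%, which sum to 34%; 112 × 0.34 = 38 complex cases. It gives no SSAVS frequency and calls the finding uncommon. The frequencies f below are assumptions.

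| Assumed f | 112 × f | Share of complex cases, f / (0.34 + f) |
|---|---|---|
| 1% | 1.1 | 3% |
| 2% | 2.2 | 6% |
| 3% | 3.4 | 8% |
| 5% | 5.6 | 13% |

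**Step 3: effect on the increment credited to NIHSS.** Simulated cohorts of 112 had 38 other complex cases and 2 to 8 stenosis patients. The assumed NIHSS distributions were gamma: shape 2.2, scale 6 (mean 13.2) in other complex cases; shape 1.5, scale 5 (mean 7.5) in stenosis patients; shape 1.2, scale 5 (mean 6.0) in the rest. CBA distributions were also assumed. The quantity is

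D = [AUC(CBA + NIHSS) − AUC(CBA)] under the plan's label − [the same difference] with stenosis patients left out.

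- D is about 0.003 to 0.013.
- For NIHSS alone, the AUC is about 0.003 to 0.011 higher under the plan's label.
- The combined CBA + NIHSS AUC is no higher under the plan's label than with stenosis patients left out.
- One cohort's AUC has a standard deviation of about 0.035 to 0.045.

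**Step 4: other comparators.**

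- A second simulation, with other assumed distributions and SSAVS at 1% to 5%, removed SSAVS from the case definition. CBA-alone accuracy in that comparison fell as stenosis became commoner (0.842 at 1%, 0.793 at 5%, mean NIHSS 4), so stenosis patients evidently stayed in as non-cases. At 5% and mean NIHSS 4, the increment was 0.920 − 0.792 = 0.128 under the plan's label and 0.907 − 0.793 = 0.114 without SSAVS, a difference of 0.014. Over 1% to 5% and mean NIHSS 4 or 6, the difference runs from 0.001 to 0.018. The combined AUC was 0.002 to 0.019 higher under the plan's label.
- Counting every stenosis patient as complex (criteria a and b only) gives larger gaps. For NIHSS alone with 34 other complex cases they are 0.787 − 0.762 = 0.025 with 4 stenosis patients and 0.791 − 0.742 = 0.049 with 8. For CBA + NIHSS in the second simulation they are about 0.01 to 0.06. This comparator changes the target, so the gaps do not measure bias.

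**The case against.** The strongest defence is that severity is a deliberate part of the SSAVS target. The Background presents complex stroke as the group needing escalation and says that SSAVS presents like LVO. NIHSS is available at triage, so its help in finding stenosis with a high score is usable there. This stands, and it is why NIHSS should not simply be barred from the model. It does not remove the need to separate diagnostic from definitional gain.

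The analysis is exploratory, NIHSS is named only as an example, and SSAVS is called uncommon. These points limit the consequence. NIHSS would probably be retained anyway, since its simulated AUC is about 0.78 with no stenosis patients at all. Even so, the protocol itself fixes both the candidate predictor and the definition, and no passage deals with the overlap.

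A reader might infer three stronger things that the documents do not support:

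- **That NIHSS alone decides the label for every stenosis patient.** The attribution process sends those with a low NIHSS and PTS to PTS, which is complex.
- **That the definition adds 0.03 to 0.05 of AUC.** That size arises for NIHSS alone, against a target that counts low-NIHSS stenosis as complex. The protocol intends those patients as non-complex.
- **That the combined model's accuracy is shown to be inflated.** The combined AUC is no higher under the plan's label than with stenosis patients left out. It is slightly higher if they are kept as non-cases. The sign depends on the comparator.

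**Conclusion.** The point holds as a limited one. For patients with side-compatible stenosis of 70% or more and no LVO, LICH or PTS, admission NIHSS sets the complex-stroke label that Objective 3(i) then asks it to predict. Part of any gain credited to NIHSS in that model is definitional.

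The part is probably small: roughly 0.003 to 0.013 in the AUC increment for 2 to 8 stenosis patients of 112, compared with leaving them out. That is well inside the sampling variation of a single cohort. The figure rests on assumed NIHSS and CBA distributions and an assumed number of stenosis patients, because the protocol gives none of these. The direction of the effect on the NIHSS increment was the same in both simulations. Nothing here touches the LVO covariate model, Objectives 1 and 2, or the sample size.

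**What to change.** Keep the complex-stroke definition and the planned covariate model. Add to Objective 3(i):

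- Whenever NIHSS is in the complex-stroke model, also report that model against LVO + LICH + PTS, leaving out patients with stenosis of 70% or more and no other complex state. An alternative is to set SSAVS by criteria (a) and (b) only, for this analysis alone.
- State that NIHSS is part of the SSAVS reference standard.
- Base any claim about the added value of NIHSS on that parallel analysis and on the LVO model.

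No new data are needed: percentage stenosis, symptom side and NIHSS are already recorded. The cost is a short addition to the text, one recoded outcome and one extra exploratory model. The downside is that this model has a slightly different target from Objective 1, and the report must say so.

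### Objective 3(i) keeps a clinical covariate only if it significantly raises the ROC AUC; with a standard paired AUC test on nested models, this would discard most weak to moderate covariates at the planned sample size

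*Protocol article*

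**What the plan says.** Objective 3(i) asks whether clinical data available at the point of testing could improve the accuracy of the device. The method is that "key variables will be added to the logistic regression models described in objectives 1 and 2", which makes each comparison one of nested logistic models on the same participants. The candidates are left open, with gender, age and NIHSS as examples. Selection is stepwise, and "only variables that significantly improve the ROC AUC will be retained in the model". The output is then stated: "Sensitivity, specificity, ROC AUC (with confidence intervals) and threshold will be reported if a suitable model is found".

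The section names neither the test of the AUC gain nor its significance level. It does state the status of the work: "This is an exploratory objective, and as such the analyses will be data-driven and dependent on results for objectives 1 and 2".

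Two other places matter. Under SSAVS outcome state, one of three joint conditions is that "the severity of the focal symptoms is ≥ 6 on the NIHSS scale (measured on admission"), and SSAVS is one component of complex stroke. Under Sample size, the case mix comes from this statement: "Reported frequencies for LVO, large intracerebral haemorrhages and prior territorial stroke are 27%, 3% and 4% respectively".

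**The concern.** The AUC gain is a poor quantity on which to base a retention test. When the added coefficient is zero, the two fitted scores rank participants almost identically, and the AUC is flat in that coefficient around zero. The AUC difference is then not approximately normal with the variance that a paired AUC test assigns to it, and the test falls far below its nominal level. With a real but moderate covariate the difference stays small relative to that variance, so power is poor. The likelihood-ratio test uses the same data and asks directly whether the covariate carries information beyond CBA.

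At stake is the answer to the objective's own question. An exploratory search should be sensitive, and this rule makes it the reverse. A reader of the results could take the absence of covariates from the final model as evidence that clinical data add nothing, when the rule could hardly have retained them.

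**Working it through.** **1. Number of cases and non-cases.** The article gives no figure for the covariate model, so the size comes from the specificity calculation.
- Complex stroke prevalence: 27% + 3% + 4% = 34% (SSAVS is given no share). Non-cases: 66%. For LVO alone: 27% and 73%.
- Specificity 85% against a minimum of 70%, alpha 0.05, power 90%: an exact one-sided binomial test needs 73 non-cases, so 73/0.66 = 110.6 (111 participants) and 73/0.73 = 100. With 74 non-cases, 74/0.66 = 112.1 and 74/0.73 = 101.4. The planned 112 and 101 are reproduced to within one participant.
- Hence 112 × 0.34 ≈ 38 complex-stroke cases and 74 non-cases. For LVO: 101 × 0.27 ≈ 27 cases, or 112 × 0.27 ≈ 30 cases and 82 non-cases.

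**2. The AUC gain to be detected.** Assume independent normal CBA and covariate with equal variances. A separation of d SD gives AUC = Φ(d/√2). CBA at 1.2 SD (assumed) gives Φ(0.849) = 0.802. Adding a covariate at s SD gives a combined separation of √(1.2² + s²).
- s = 0.5: √1.69 = 1.300, AUC 0.821, gain 0.019.
- s = 0.7: √1.93 = 1.389, AUC 0.837, gain 0.035.
- s = 1.0: √2.44 = 1.562, AUC 0.865, gain 0.063.
- s = 1.5: √3.69 = 1.921, AUC 0.913, gain 0.111.

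**3. Retention by the two tests.** Simulated data with 38 cases and 74 non-cases and CBA AUC about 0.80; CBA alone against CBA plus one covariate; two-sided 0.05; 1,500 to 2,000 runs per setting in the main sets. Ranges span separate sets of runs.

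| Covariate separation (own AUC) | Paired AUC test (DeLong) | Likelihood-ratio test |
|---|---|---|
| none (0.50) | 0–0.1% | 4–7% |
| 0.3 SD (0.58) | 0.9% | 27% |
| 0.5 SD (0.64) | 4–6% | 56–58% |
| 0.7 SD (0.69) | 19–21% | 84–87% |
| 0.8 SD (0.71) | 30% | 92% |
| 1.0 SD (0.76) | 58–61% | 98–99% |
| 1.5 SD (0.86) | 96–97% | 100% |

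If CBA's own AUC varies from 0.70 to 0.90, AUC-test power is 0.3–11% for covariates with own AUC 0.58–0.64 (likelihood ratio 19–67%) and 10–76% for own AUC 0.71–0.76 (likelihood ratio 79–100%).

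**4. What the replacement does to optimism.** Forward selection from 10 candidates, one real at 0.8 SD, threshold set for about 70% sensitivity as in objective 1, 400 runs at 38/74.
- AUC rule: some variable selected in 31% of runs. In those runs, apparent AUC is 0.866 against 0.843 in new data; sensitivity is 71% against 66%.
- Likelihood-ratio rule: selected in 96% of runs. Apparent AUC is 0.855 against 0.826; sensitivity is 71% against 66%.
- Averaged over all runs, AUC optimism is 0.011 under the AUC rule and 0.029 under the likelihood-ratio rule. With 20 pure-noise candidates (200 runs) it is 0.000 and 0.049.

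At LVO size (30/82, 10 candidates, one real at 0.8 SD, 200 runs), the AUC rule selects something in 23% of runs and the likelihood-ratio rule in 94%.

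**The case against.** - **Strong covariates get through.** This stands. A reader might infer that the rule has almost no power at all. It does not: retention is about 60% at 1.0 SD and 96–97% at 1.5 SD. NIHSS may be a strong covariate, since Objective 3(ii) treats RACE as the most accurate clinical scale for LVO and computes it from NIHSS items. The article gives no accuracy figure for NIHSS, so a wrong negative answer for that variable is not shown.
- **The test is not named.** This stands as a limit. The figures hold for a DeLong-type paired test, and an unseen analysis plan could specify another. The retention criterion itself, significance of the AUC gain, is fixed in the text.
- **The analysis is exploratory.** This stands and limits the consequence. It does not justify a selection rule whose false-retention rate is about 0.1%.
- **Accuracy of the selected model.** A reader might infer that it will be reported without correction for optimism. The article is silent, and internal validation may sit in the full protocol or analysis plan, so this is not a finding. Nor should inflation from selecting noise variables by likelihood ratio be charged to the plan, because its own rule admits almost no noise.
- **NIHSS and SSAVS.** A reader might infer that NIHSS predicts complex stroke largely by definition. The overlap is real but unquantified. It is absent from the LVO definition and is probably small, because the Sample size section describes SSAVS as uncommon.

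**Conclusion.** The concern holds for the retention rule. With a paired AUC test on nested models, the rule works at about 0.1% instead of 5%. At about 38 cases and 74 non-cases it keeps a 0.5 SD covariate in 4–6% of runs against 56–58% by likelihood-ratio test, and a 0.7 SD covariate in about 20% against 84–87%. At 1.0 SD the loss shrinks to about 60% against 98%. The exploratory answer is therefore biased towards no added value for moderately useful clinical variables.

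This rests on assumptions that are not in the article: the DeLong test, a two-sided 0.05 level, independent normal variables, and a CBA AUC near 0.80. The direction is the same over a CBA AUC of 0.70–0.90. The objective 1 and 2 results at CBA = 10 do not depend on this rule.

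**What to change.** 1. Replace the AUC-significance criterion with a short pre-specified list (for example age, sex and NIHSS) entered together with CBA. Judge added value by the likelihood-ratio test at a stated level, or use penalised regression.
2. Report the change in AUC as an estimate with its interval, not as the gate for retention.
3. State that AUC, and sensitivity and specificity at the chosen threshold, will be bootstrap-corrected for optimism, with any selection and the threshold choice repeated in each resample. This belongs with the first change, because likelihood-ratio selection lets more variables in.
4. Minor: when NIHSS is in the complex-stroke model, repeat the model without the SSAVS cases.

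The cost is wording and a bootstrap, with no new data. Reported accuracy of the extended model will be slightly lower.
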